# 4.3 Sample Size and Analysis

This study is designed to compare the change (day 28 less baseline) in the percentage of CD4 positive T cells expressing Ki67 between the two treatment groups. Randomization will be 2:1 favoring leflunomide.

Using historical data, a conservative estimate of the standard deviation of the change is 0.60 and a conservative estimate of the mean is 4.0. To detect a 30% drop in the mean to 2.8 from 4.0 with 90% power using a two-sided t-test with type 1 error rate set to 0.05 requires 10 patients in the leflunomide arm and 5 patients in the placebo arm.

With 1:1 randomization, 7 patients per arm are required to achieve the above parameters. However, with a 2:1 randomization, the standard error of the change in the leflunomide arm is reduced by 17% relative to a 1:1 randomization. Since the difference in total sample size for a 2:1 versus 1:1 randomization is minimal and precise estimation of the change in the leflunomide group desired, this study will use a 2:1 randomization. To allow for 20% dropout, 18 patients will be recruited: 12 in the leflunomide arm and 6 in the placebo arm. In order to enroll 18 patients, the total accrual ceiling will be 40, to account for patients who may screen but not enroll.

The primary analysis will be performed as treated using a t-test. Secondary analyses will be evaluated using tests and descriptive statistics, as appropriate. Analyses will also be performed as intent to treat. Assumptions for statistical procedures will be examined and appropriate alternatives will be used as necessary, e.g. log transformations or nonparametric methods.

#

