# 2. 0 Hypothesis

At 28 days, HIV-1 infected patients who receive leflunomide 20 mg daily will have lower levels of CD4+ T cell proliferation, as measured by mean percentage of CD4+ cells which express Ki67, compared to HIV-1 infected patients who receive placebo.

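### Section 4.3 fixes an unadjusted t-test on the change in % Ki67 and leaves it replaceable without a rule; adjusting for the Day 1 value, with the scale settled before unblinding, is a better primary analysis at almost no cost

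*Protocol*

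**What the plan says.** Section 4.3 defines the primary comparison: "This study is designed to compare the change (day 28 less baseline) in the percentage of CD4 positive T cells expressing Ki67". The target is set out as "To detect a 30% drop in the mean to 2.8 from 4.0", with "a conservative estimate of the standard deviation of the change is 0.60", and the trial is sized "with 90% power using a two-sided t-test with type 1 error rate set to 0.05". This leads to 10 leflunomide and 5 placebo patients, or 7 per arm under equal allocation, and recruitment of 12 and 6 to allow for dropout. The primary test is a t-test; no covariate is named.

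The section closes by saying that assumptions will be examined and that "appropriate alternatives will be used as necessary, e.g. log transformations or nonparametric methods". It does not say what would trigger a replacement, which alternative comes first, or whether the person choosing would be blind to arm.

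Two other places bear on this. Section 4.4.2 has blood drawn before the first dose on Day 1, and that sample is the baseline for Ki67. Section 4.4.3 unblinds each patient's arm on Day 29, the visit at which the end-of-treatment Ki67 sample is drawn.

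**The concern.** **Baseline.** A change score subtracts the whole of the Day 1 value. When the correlation between the two visits is below 1, that over-corrects: a patient who starts high by chance tends to fall anyway. With about 10 against 5 patients, the arms can differ noticeably at Day 1 by chance, and part of that difference passes into the estimated effect. A regression on Day 1 Ki67 removes it, and the data are already collected.

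**Replacement.** The primary test can be exchanged under a clause with no rule, in a trial where the arm is disclosed patient by patient as the endpoint is collected. Nothing in section 4.3 excludes a choice made with the arms known. If the log option were used, the primary quantity would also change from a difference in percentage points to a ratio.

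At stake are some precision in a very small trial and confidence that its one primary result came from a rule fixed in advance.

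**Working it through.** **Inputs from section 4.3.** Reference mean 4.0; target mean 2.8; SD of the change 0.60; two-sided alpha 0.05; evaluable patients 10 and 5.

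**Step 1: the plan's own figure.** Difference = 4.0 − 2.8 = 1.2 points; standardised, 1.2/0.60 = 2.0. Exact t-test power uses noncentrality 1.2 / (0.60 × √(1/n₁ + 1/n₂)) on n₁ + n₂ − 2 degrees of freedom.

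| Leflunomide + placebo | Power |
|---|---|
| 8 + 4 | 0.837 |
| 10 + 5 | 0.921 |
| 12 + 6 | 0.963 |
| 6 + 6 | 0.876 |
| 7 + 7 | 0.929 |

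Both stated sizes are confirmed: 10+5 is the smallest exact 2:1 split reaching 90%, and 7 per arm the smallest equal split.

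**Step 2: what adjustment would give.** Assume the same SD, s, at both visits, correlation ρ between them, and an additive effect.

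- Variance of the change: 2s²(1 − ρ) = 0.36, so s = 0.60/√(2(1 − ρ)).
- Residual variance after regression on Day 1: s²(1 − ρ²) = 0.36 × (1 + ρ)/2.
- Chance imbalance in the covariate multiplies the variance of the adjusted difference by 1 + 1/(N − 4) on average. At N = 15 this is 1 + 1/11 = 12/11.
- Ratio of standard errors, adjusted to change score: √[(1 + ρ)/2 × 12/11].
- Degrees of freedom fall from 13 to 12.

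The powers below are simulated at 10+5. The formula agrees with them to about 0.002.

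| ρ (assumed) | Implied s | SE ratio | Adjusted power | t-test power |
|---|---|---|---|---|
| 0.3 | 0.51 | 0.84 | 0.98 | 0.92 |
| 0.5 | 0.60 | 0.90 | 0.96 | 0.92 |
| 0.7 | 0.77 | 0.96 | 0.93 | 0.92 |
| 0.8 | 0.95 | 0.99 | 0.92 | 0.92 |
| 0.9 | 1.34 | 1.02 | 0.91 | 0.92 |

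Type I error was close to 5% for both methods. The standard errors are equal when (1 + ρ)/2 × 12/11 = 1, that is ρ = 22/12 − 1 = 0.83. With the lost degree of freedom, the powers meet at about 0.8.

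**Step 3: size of the imbalance.** At ρ = 0.5, s = 0.60, so the Day 1 difference between arms has standard error 0.60 × √(1/10 + 1/5) = 0.33 points. A one-standard-error imbalance shifts the change-score estimate by (1 − ρ) × 0.33 = 0.16 points, or 0.16/1.2 = 14% of the target effect.

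**Step 4: the log alternative.** With a mean change of −1.2 and SD 0.60, and assuming normality, the expected share of negative changes under leflunomide is Φ(1.2/0.60) = Φ(2) = 0.98. If placebo is stable, about half of the placebo changes are negative. None of these can be logged. The percentages themselves can be logged before differencing, but the contrast is then a ratio.

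**The case against.** The strongest reply is that nothing here is wrong. A t-test on change is valid under randomisation, the baseline is used through subtraction, and the sample size is right. Covariates and the rule for alternatives are often left to a statistical analysis plan, which is not at hand. All of this stands, and it limits the point to an improvement. It does not remove it: section 4.3 itself names the unadjusted test and itself permits its replacement.

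Four stronger readings are tempting, and the documents do not support them.

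- *The test does not match a proportional 30% effect.* Section 4.3 converts the 30% to 1.2 points and pairs it with the SD of the change, so effect, SD and test share one absolute scale. The 30% describes the group mean; nothing says each patient falls by 30%.
- *A log-scale model gains a great deal of power.* In simulations with lognormal levels and a multiplicative effect at 10+5, log-scale adjustment reaches 98–99%, against 94/93/90/86% for the t-test at between-patient CVs of 20/30/40/50%. The protocol gives no CV, and that model is the one the log analysis assumes. Even so, the t-test meets 90% in three of the four cases.
- *Section 2 contradicts section 4.3.* Section 2 frames the hypothesis at 28 days, "as measured by mean percentage of CD4+ cells which express Ki67", rather than as a change. Under randomisation the expected baselines are equal, so levels and changes estimate the same contrast.
- *The replacement clause inflates type I error.* Rates of about 6.2–7.4% arise only if the smallest of three p-values (t-test on change, t-test on log ratio, rank test) is taken, which the protocol does not propose. A switch triggered by a normality test of residuals, itself an assumed rule, gave 4.9–5.4% at 12+6. Nor does the protocol say the choice follows unblinding; it only fails to exclude that.

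**Conclusion.** The point holds as an efficiency gain and a safeguard. The stated sample size need not change.

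At 10+5, adjustment changes power from 0.92 to between 0.98 (ρ = 0.3) and 0.91 (ρ = 0.9). It helps clearly at low to moderate correlation, is neutral near 0.8, and costs roughly one to two points at 0.9 or above. These figures assume an additive effect, equal variances at the two visits, and correlations that the protocol does not supply. Whatever the correlation, adjustment accounts for chance Day 1 imbalance against 5 or 6 placebo patients.

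The open replacement clause is a real but minor supporting point. It leaves room for an unblinded choice of primary test, and its log option does not fit the endpoint as defined. No inflation of type I error can be attributed to the plan as written.

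**What to change.** In section 4.3:

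1. Make the primary analysis a linear model of end-of-treatment % Ki67 (or, equivalently for the arm effect on the raw scale, its change) on arm, with Day 1 % Ki67 as covariate. Report the adjusted difference with its 95% confidence interval.
2. Choose the scale once, before any patient is unblinded. If the log scale is chosen, log the Ki67 levels at both visits and state that the result is a ratio.
3. Keep the t-test on change and a rank test as labelled sensitivity analyses that cannot replace the primary result. Confine the general clause on alternatives to secondary analyses.

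The cost is a few sentences, one degree of freedom, and a possible power loss of one to two points if the correlation is 0.9 or higher. No extra patients, visits or assays are needed.

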In addition, safety and research labs will be performed as at other clinic visits. Any other testing will be performed as clinically indicated.

If a patient ends study due to a drop in CD4+ T cell count, the patient’s CD4+ T cell count will be monitored following the leflunomide elimination procedure. If the CD4+ T cell count remains decreased 10 – 14 days after the elimination procedure is completed, the patient will be referred to their primary care physician for further monitoring and consideration of treatment with antiretrovirals, depending on their actual CD4+ T cell count and viral load.

If patients withdraw from study prior to receiving study drug, they will be replaced by enrolling new patients in their place. This refers only to patients who withdraw prior to receiving study drug and whose treatment arm has not been unblinded to either the subject or the study team.

If a patient withdraws from study for any reason, every effort will be made to attain complete data from that patient, including endpoint data at Day 29.

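### Eighteen patients cover about 17% dropout, not the stated 20%: a minor misstatement in Section 4.3 that does not show an underpowered trial

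*Protocol*

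**What the plan says.** Protocol Section 4.3 (Sample Size and Analysis) plans a comparison of the change in the percentage of CD4+ T cells expressing Ki67. The planning inputs are:

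- Test: "two-sided t-test with type 1 error rate set to 0.05", with 90% power.
- Difference: "To detect a 30% drop in the mean to 2.8 from 4.0".
- Variability: "a conservative estimate of the standard deviation of the change is 0.60".
- Allocation: "Randomization will be 2:1 favoring leflunomide".

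The section concludes that this "requires 10 patients in the leflunomide arm and 5 patients in the placebo arm", and then sets the enrolment: "To allow for 20% dropout, 18 patients will be recruited: 12 in the leflunomide arm and 6 in the placebo arm". It gives no formula for the dropout step. It also sets an accrual ceiling of 40, which it ties to patients who are screened but not enrolled.

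Two rules in Section 6.3 bear on losses. The first is "If patients withdraw from study prior to receiving study drug, they will be replaced by enrolling new patients in their place"; it is limited to patients whose arm has not been unblinded to the subject or the study team. The second commits the team to seek full data, including the Day 29 endpoint, from anyone who withdraws.

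**The concern.** A dropout allowance should answer one question: if the stated fraction of recruited patients is lost, does the required number remain? Here the recruited number equals the requirement increased by 20%. That is not the same as a number that still meets the requirement after 20% is removed. The sentence is the protocol's only justification for enrolling 18, and a reader would use it to judge how many losses the comparison can absorb. With six placebo patients planned and five required, that arm has room for one loss, so the exact allowance matters more than it would in a larger trial.

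**Working it through.** **Inputs (all Section 4.3).** Two-sided α = 0.05; difference δ = 4.0 − 2.8 = 1.2; SD of the change σ = 0.60, so δ/σ = 2; allocation 2:1; required 10 + 5 = 15; dropout d = 20%; recruited 12 + 6 = 18.

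**Step 1: reproduce the requirement.** Power comes from the noncentral t distribution with n₁ + n₂ − 2 degrees of freedom and noncentrality δ / [σ√(1/n₁ + 1/n₂)].

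| Evaluable (leflunomide + placebo) | Power |
| --- | --- |
| 8 + 4 | 83.7% |
| 10 + 5 | 92.1% |
| 6 + 6 | 87.6% |
| 7 + 7 | 92.9% |

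So 10 + 5 is the smallest exact 2:1 design reaching 90%, and 7 per arm is the smallest 1:1 design. Both agree with the protocol. Rounding up leaves 10 + 5 with about two points of slack.

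**Step 2: reproduce the recruited number.** N × (1 + d) = 15 × 1.2 = 18; by arm, 10 × 1.2 = 12 and 5 × 1.2 = 6. This gives the protocol's figures exactly.

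**Step 3: the number that 20% dropout implies.** N / (1 − d) = 15/0.8 = 18.75, so 19. By arm, 10/0.8 = 12.5 and 5/0.8 = 6.25, so 13 + 7 = 20 if each arm is rounded up separately. The stated 18 is 0.75 patient short before rounding, and 1 or 2 short after it.

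**Step 4: what 18 covers.** Expected number left at 20% loss: 12 × 0.8 = 9.6 and 6 × 0.8 = 4.8, together 14.4, against 10 + 5 = 15. The loss that leaves exactly 15 is 3/18 = 16.7%, and it leaves 10 + 5 only if two losses are on leflunomide and one on placebo.

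**Step 5: what this does to power.** Same formula and inputs as Step 1:

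| Evaluable | Power |
| --- | --- |
| 10 + 5 (the stated requirement) | 92.1% |
| 9.6 + 4.8 (expected at 20% loss) | 90.8% |
| 9 + 5 | 90.8% |
| 10 + 4 | 87.3% |

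If each of the 12 + 6 patients is lost independently with probability 0.20, power averaged over the resulting binomial distributions is 89.2%. Independence is an assumption of this check; the protocol does not say how losses arise.

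**The case against.** The strongest reply is that the slip has almost no consequence. Because 10 + 5 already exceeds 90%, power at the expected retained numbers is still 90.8%. It falls below 90%, to about 89%, only after averaging over an assumed binomial loss. Section 6.3 also softens the practical risk: patients lost before dosing and still blinded are replaced, and stopping drug early need not mean losing the Day 29 measurement. All of this stands, and it fixes the size of the point. It does not make the sentence right. Losses after dosing are not replaced, the accrual ceiling of 40 is for screening failures, and 20% is the protocol's own planning rate.

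Two stronger readings are tempting, and the documents support neither.

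- A reader might infer that the trial misses its 90% power at its own dropout rate. The expected-number result is above 90%, and the averaged result is under one point below it and depends on an unspecified loss mechanism. The chance of keeping at least 10 and at least 5 under independent 20% loss is low (about 37%), but that asks for full retention of the requirement in each realisation, whereas an allowance normally covers the expected loss.
- A reader might infer that the statement in the same paragraph that "the standard error of the change in the leflunomide arm is reduced by 17% relative to a 1:1 randomization" is also wrong, since 1 − √(7/10) = 16.3%. The protocol does not say that rounded numbers were used. Solving for exactly 90% power gives 6.39 per arm at 1:1 and 9.37 on leflunomide at 2:1, and 1 − √(6.39/9.37) = 17.4%. The 17% is thus reproducible at equal power. The 13% obtained from 1 − √(7.5/10) compares designs of equal total size, which is not the comparison the paragraph makes.

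**Conclusion.** The dropout statement in Section 4.3 is wrong as written: 18 patients allow for three losses (16.7%), not 20%. The error is small. The expected shortfall is 0.6 patient after 20% loss (14.4 against 15), or 0.75 patient in the number to recruit. Power at 20% dropout is about 89 to 91%, depending on whether losses are averaged or taken at their expectation, and 87.3% if 14 patients remain as 10 + 4. This is a minor misstatement of the margin; it does not show that 18 is too few or that the trial is underpowered. The power figures take the protocol's difference of 1.2 and SD of 0.60 as given; the lower end of the range also assumes independent losses.

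**What to change.** Keep 18 patients and restate the allowance in Section 4.3, for example: *Eighteen patients allow for about 17% dropout (2 leflunomide, 1 placebo); at 20% dropout power is about 89 to 91%.* Leave the 17% standard-error figure unchanged.

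The cost is one sentence, with no added patients and no change to procedures or analysis. If the sponsor prefers to keep the 20% claim, the matching enrolment is 19, or 20 (13 + 7) with each arm rounded up, but the small shortfall does not require it.

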## **4.4 Procedures**

**4.4.1 Screening period**

After signing screening informed consent, subjects will be evaluated in clinic to determine eligibility. At the time of the screening visit, the subject history will be reviewed and the following procedures will be performed (see Table 1):

- HIV testing
- Urine pregnancy testing for women of child-bearing potential (serum can be used for pregnancy testing in the event that urine is not collected)
- HIV viral load
- CD4+ and CD8+ T cell counts
- HLA testing
- Safety labs:
  - CBC with differential
  - acute care panel (sodium, potassium, chloride, bicarbonate, creatinine, urea nitrogen, creatinine)
  - hepatic panel (ALT, AST, alkaline phosphatase, total bilirubin, direct bilirubin)
  - mineral panel (albumin, calcium, magnesium, phosphorus)
  - amylase and lipase
  - PT and PTT
  - urinalysis
  - hepatitis screen (Hepatitis B surface antigen, anti-Hepatitis C antibody, hepatitis C PCR)
  - lipid panel (total cholesterol, triglycerides, HDL cholesterol, LDL cholesterol)
- EKG – (if patient can provide an EKG performed within 3 months of screening, the EKG will be deferred)
- CXR – (if patient can provide a CXR performed within 3 months of screening, the CXR will be deferred)

If the subject is determined to be eligible, he or she will be seen in clinic again for a history and comprehensive physical exam. The comprehensive physical exam includes weight, height, temperature, pulse, blood pressure, respiratory rate, pulse oximetry, and examination of the following:

- General appearance
- Skin
- Head, eyes, ears, nose, throat
- Neck
- Chest and lungs
- Heart
- Abdomen
- Extremities
- Cranial nerves, motor and sensory assessment

Blood will be drawn for repeat of safety labs (except hepatitis screen and lipids), HIV viral load and CD4+ and CD8+ T cell counts, urine will be sent for pregnancy testing and the subject will then sign the standard informed consent.

The screening period (time between signing screening informed consent and Day 1) will be no longer than 28 days.

After signing the standard informed consent, patients will be randomized to receive leflunomide or placebo. Randomization will be computer generated by the clinical center pharmacy staff. No one on the study team or the patient will have access to the randomization assignment until scheduled unblinding or earlier if clinically indicated for patient safety.

**4.4.2 Treatment period (Day 1 through 28)**

Patients must have stopped taking contraindicated medications one week prior to Day 1 (see Appendix A - Medications Metabolized by CYP 2C9 and Contraindicated During Treatment Period). Day 1 through 28, patients will receive leflunomide 20 mg orally, once daily or placebo. If appropriate, a urine pregnancy test will be performed on Day 1 before delivery of study drug.

On Days 1 and 15 of study, patients will return for clinic visits (it will be sufficient if patients come within plus or minus 2 days of each study visit during the treatment period and within plus or minus 7 days during the post-treatment follow up period). At these visits their history will be reviewed and they will undergo a targeted physical exam to be driven by any signs or symptoms identified by the patient. The targeted physical exam will also include temperature, pulse, blood pressure, respiratory rate and examination of the heart, lungs and abdomen. Patients will have urine sent for pregnancy testing if appropriate and blood drawn for safety labs, HIV viral load, CD4+ and CD8+ T cell counts, expression of Ki67, expression of activation markers, memory/naïve phenotyping, expression of coreceptors (CCR5 and CXCR4), ELISA for IL-7, TNF level, lymphoproliferative responses, Annexin V staining and *ex vivo* BrdU. Additionally, blood will be drawn for measurement of the main metabolite of leflunomide, M1 or A77 1726. On Day 1, blood will be drawn for these labs prior to administration of medication so that these values will serve as baseline values.

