**4.4.3 Post-treatment follow up period (Day 29 through 64)**

On Day 29, the patient’s treatment arm will be unblinded. Patients who were receiving placebo will end study on Day 29. Patients who were receiving leflunomide will begin the drug elimination procedure: cholestyramine 8 grams orally three times a day for 11 days over the following 14 days. On Day 43, a serum A77 1726 level will be measured to assure elimination of the drug metabolite from the serum. Drug level should be less than 0.02 mg/L (or 0.02 ug/mL). If A77 1726 is less than 0.02 mg/L, the patient will end study on Day 64. If the level is above 0.02 mg/L, the 11 day cholestyramine elimination procedure will be repeated, and the study period will be extended as needed.

During the post-treatment follow up period, patients will come in for study visits on Days 29, 43 and 64. On these days, they will have their histories reviewed, urine will be sent for pregnancy testing when appropriate, and blood will be drawn for safety labs, HIV viral load, CD4+ and CD8+ T cell counts. On Days 29 and 43, blood will also be drawn for research studies of lymphocytes including expression of Ki67, expression of activation markers, memory/naïve phenotyping, expression of coreceptors (CCR5 and CXCR4), ELISA for IL-7, TNF level, lymphoproliferative responses, Annexin V staining and *ex vivo* BrdU as well as for measurement of A77 1726. On Days 29 and 43 they will undergo comprehensive physical exams and on Day 64 a targeted physical exam.

Table 1. Procedures

|  | Scr | H&P | D11 | D15 | D29 | D432 | D642 |
| --- | --- | --- | --- | --- | --- | --- | --- |
| Screening consent | X |  |  |  |  |  |  |
| Standard consent |  | X |  |  |  |  |  |
| History | X | X | X | X | X | X | X |
| Comprehensive physical exam |  | X |  |  | X | X |  |
| Targeted physical exam |  |  | X | X |  |  | X |
| EKG and CXR | X |  |  |  |  |  |  |
| HLA testing | X |  |  |  |  |  |  |
| Safety labs3 | X | X | X | X | X | X | X |
| Urine pregnancy test4 | X | X | X | X | X | X | X |
| HIV ELISA5 | X |  |  |  |  |  |  |
| Hep B, C serology6 | X |  |  |  |  |  |  |
| Lipid panel | X |  |  |  |  |  |  |
| HIV viral load | X | X | X | X | X | X | X |
| Flow cytometry | X7 | X7 | X8 | X8 | X8 | X8 | X7 |
| Additional studies9 |  |  | X | X | X | X |  |
| A77 1726 level |  |  | X | X | X | X |  |

1. On Day 1, blood will be drawn prior to administration of study drug

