**8.1 Data Safety Monitoring Board**

The NIAID Data Safety Monitoring Board (DSMB) will be asked to monitor the progress of the study while still blinded to the investigators. The NIAID Intramural DSMB is constituted to review the safety data of all NIAID-sponsored clinical studies that require DSMB oversight and consists of experts in infectious diseases, biostatistics, and clinical trials. The DSMB will review cumulative study data twice per year to evaluate safety, study conduct, and scientific validity and integrity of the trial. As part of this responsibility, DSMB members must be satisfied that the timeliness, completeness, and accuracy of the data submitted to them for review are sufficient for evaluation of the safety and welfare of study participants. The DSMB will also assess the performance of the overall study operations and any other relevant issues as necessary.

In addition to the biannual meetings, the DSMB will meet to review the data when 8 patients (47% of total expected enrollment) have been enrolled and have completed the treatment period. The group will also convene on an urgent basis if two or more subjects meet criteria for stopping study drug (see **section 6.3**) due to toxicities.

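### The only end-of-treatment Ki67 draw (Day 29) is classed as a follow-up visit and so carries a ±7-day window, wider than the ±2 days given to Day 15

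*Protocol*

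**What the plan says.** Section 4.3 defines the primary comparison through "the change (day 28 less baseline", that is, with Day 28 as the end point. Dosing runs from Day 1 through Day 28 (Section 4.4.2).

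Section 4.4.2 names the treatment-period visits ("On Days 1 and 15 of study, patients will return for clinic visits") and sets two windows in one sentence. Visits such as these are allowed "within plus or minus 2 days of each study visit during the treatment period". The wider allowance, for later visits, is "within plus or minus 7 days during the post-treatment follow up period".

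Section 4.4.3 covers Days 29 through 64 and states: "During the post-treatment follow up period, patients will come in for study visits on Days 29, 43 and 64". Table 1 has no Day 28 column, so Day 29 is the first Ki67 draw after Day 15. Section 6.3 refers to endpoint data at Day 29, and Section 4.2.2 uses Day 29 as end of treatment for viral load.

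Also on Day 29, the patient's "treatment arm will be unblinded" (Section 4.4.3), placebo patients leave the study and leflunomide patients begin cholestyramine. For Day 1, Section 4.4.2 and the Table 1 footnote require blood before study drug. No comparable order is set for Day 29.

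**The concern.** A visit that closes the treatment period has been filed under follow-up and takes the follow-up window. The measurement that decides the trial is therefore timed more loosely than the mid-course measurement.

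Timing matters because drug exposure changes around that date. Before Day 29 the metabolite is still accumulating. After Day 28 dosing has stopped, and the elimination procedure then shortens the half-life from about two weeks to one day (Section 1.4). Placebo patients have no exposure to lose, so mistimed draws act on the leflunomide arm only. They pull its mean change toward placebo and add some spread. With 18 patients and one end-of-treatment draw each, there is little to average this out. A statistical analysis plan can exclude or flag a mistimed sample, but it cannot supply the correctly timed one.

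**Working it through.** **Inputs, all from the protocol**
- Windows: ±2 days (treatment period) and ±7 days (post-treatment), Section 4.4.2.
- Dosing on Days 1 to 28, once daily; half-life about 14 days, or 1 day on cholestyramine (Sections 4.4.2 and 1.4).
- Difference 4.0 − 2.8 = 1.2; SD of change 0.60; two-sided 0.05; 10 leflunomide and 5 placebo patients (Section 4.3).

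**Step 1: the plan's own sample size.** For a two-sample t-test the non-centrality is λ = Δ / [SD × √(1/n₁ + 1/n₂)]. With 10 and 5, λ = 1.2 / (0.60 × √0.3) = 1.2 / 0.3286 = 3.65 on 13 degrees of freedom, giving power of 92.1%. With 8 and 4 it is 83.7%. So 10 and 5 is the smallest exact 2:1 split reaching 90%, and the stated figure reproduces.

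**Step 2: the permitted dates.** Day 29 ± 7 gives Day 22 to Day 36, 15 calendar days. Day 29 ± 2 would give Day 27 to Day 31.

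**Step 3: metabolite level at those dates.** Assumed model: first-order accumulation, equal daily doses, no loading dose. After n daily doses the level as a fraction of steady state is 1 − 2^(−n/14).
- Day 22, after 21 doses: 1 − 2^(−1.5) = 0.646.
- Day 29, after 28 doses: 1 − 2^(−2) = 0.750.
- Day 36, seven days after Day 29 and eight days after the last dose, no cholestyramine: 0.750 × 2^(−7/14) = 0.530.

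Relative to Day 29 this is 0.646 / 0.750 = 86% at Day 22 and 0.530 / 0.750 = 71% at Day 36. Averaged over the 15 permitted days it is 88%. Within Day 27 to 31 the lowest values are 97% at Day 27 and 91% at Day 31, again without cholestyramine.

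**Step 4: illustration of power.** The protocol does not say how Ki67 tracks the metabolite. Assume the effect is proportional to exposure.

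| Timing of draws | Mean difference | λ (10 and 5) | Power, 10 and 5 | Power, 12 and 6 |
|---|---|---|---|---|
| All on Day 29 | 1.20 | 3.65 | 92% | 96% |
| Spread evenly, Day 22 to 36 | 1.06 | 3.22 | 85% | 91% |
| All at Day 22 (bound) | 1.03 | 3.15 | 83% | 90% |
| All at Day 36 (bound) | 0.85 | 2.58 | 67% | 76% |

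The last column uses the recruited numbers with no dropout. In the even-spread case the added variance is small: the SD in the leflunomide arm rises from 0.60 to about 0.61. Simulating that case with the added spread included gives 84%.

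**Step 5: is the narrower window enough alone?** If cholestyramine had started on calendar Day 29, a Day 31 draw would be at 0.5² = 25% of the Day 29 level. The order of events therefore needs stating as well as the window.

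**The case against.** **The early edge may be unintended.** A visit on Days 22 to 28 falls inside the dosing period, where ±2 days is the stated allowance. It would also imply opening the code while dosing continues. This is fair: a 21-dose endpoint draw is probably not what the authors meant. But the text attaches the window to the visit, and Day 29 is a listed follow-up visit. The late edge is untouched by this argument.

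**The power loss is a bound on an undocumented assumption.** This stands. A reader might infer that 67% is the expected power. It is not: it needs every visit at Day 36 and an effect proportional to exposure. Visits clustered near Day 29 would lose less than the even-spread case.

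**Almost no drug at a late draw.** A reader might infer that under 1% would remain at Day 36, since seven one-day half-lives give 0.5⁷ = 0.8%. That requires cholestyramine to start on calendar Day 29 while the visit slips by a week. Section 4.4.3 puts unblinding, cholestyramine start and the placebo patient's exit on the same day as the visit, so they may well move together. The text allows the calendar reading but does not require it. For a draw later on the day cholestyramine starts, the loss is only part of the 40% fall at 24 hours reported in Section 9.3.1.2.

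**Exposure is measured.** A77 1726 is drawn at the same visit, and Section 6.2 plans to correlate levels with the endpoints. Off-exposure samples could therefore be identified, but that does not restore the planned t-test comparison.

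**Blinding.** A reader might see a contradiction with Section 8.1, where the DSMB is to "monitor the progress of the study while still blinded to the investigators". Section 4.4.1 provides for scheduled unblinding, and Section 8.1 concerns review of the ongoing study, so no contradiction is shown. Blinding the staff who read the flow data would be a preference; the documents do not show that its absence is an error.

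**Conclusion.** The point holds as a timing defect. The wording gives the sole end-of-treatment Ki67 draw a window from Day 22 to Day 36, wider than that of Day 15, and no other section narrows it. It also leaves open whether the draw precedes unblinding and the elimination procedure. The permitted dates follow directly from the text. The exposure figures of 86% and 71% rest on the stated half-life and a simple accumulation model.

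The effect on power is illustrative. Under proportionality and evenly spread visits it is a loss of about 7 percentage points at 10 and 5 patients (92% to about 85%), with 83% and 67% as edge bounds. The documents do not support a claim that the primary comparison would fail, that drug would be absent at the draw, or that the blinding provisions contradict each other.

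**What to change.** In Section 4.4.2 and Table 1, give the Day 29 endpoint visit the ±2-day window already used for treatment-period visits, and keep ±7 days for Days 43 and 64.

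In Section 4.4.3, state, as is already done for Day 1, that at the scheduled Day 29 visit the endpoint blood is drawn before the arm is opened and before any elimination-procedure dose. This is a rule about when blood is taken. It does not set when the elimination procedure begins, and it is not meant to touch the early-stopping provisions of Section 6.3.

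The sponsor should reconcile Sections 4.3, 4.4.2 and 4.4.3 on two matters: whether the primary endpoint is at Day 28 or Day 29, and whether Day 29 for the elimination procedure means the calendar day or the actual visit. No clinical timing is proposed here.

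The cost is a short amendment and slightly less scheduling flexibility at one visit. The sample size does not change.
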